## Abstract

**Background::**

In South Korea, a few patients with low back pain (LBP) are currently being treated with a combination of traditional Korean medicine (KM) and Western medicine (WM). Although a recent research has reported results regarding patient satisfaction and exploratory effectiveness, evidence of comparative effectiveness still needs to be reviewed. The aim of this study is to evaluate the clinical and cost-effectiveness of KM and WM collaborative treatment (CT) compared with that of sole treatment (ST) for patients with LBP in Korea.

**Method/design::**

This multisite, prospective observational comparative effectiveness research study is part of a nationwide pilot project for KM and WM collaboration launched by the Korean Ministry of Health and Welfare. The duration of the study is 8 weeks, and the target number of inclusion is 360 patients. Participants receive treatment according to their treatment plan, and a researcher conducts investigations thrice, every 4 weeks. In the final analysis, the merged data from the participants’ questionnaire responses, hospital medical records, and administrative data, and Health Insurance Review and Assessment service data will be compared between the CT and ST groups.

**Discussion::**

This study will provide clinical and economic information about CT for LBP, which might be a milestone for establishing future polices about this collaboration in Korea.

**Trial registration::**

The study protocol has been registered with the Clinical Research Information Service (KCT0002827).

## Introduction

1

Low back pain (LBP) is reportedly one of the most burdensome ailments in South Korea, 2013.^[1]^ In addition, a study has shown that LBP affects approximately 540 million people worldwide,^[2]^ and another study revealed that the loss of working hours due to LBP has increased by 54% between 1990 and 2015.^[3]^

In Korea, a few patients with LBP use traditional Korean medicine (KM) and Western medicine (WM) collaboratively, known as a collaborative treatment (CT). This is a special treatment system in Korea, which has dual medical systems. In CT, a medical doctor (MD) and traditional Korean medical doctor (KMD) cooperate and conduct the examination and determine the diagnosis and treatment for the patient.^[4,5]^

Although a survey demonstrated that 66.1% of the general population in Korea were aware of CT and 89.4% intended to reuse it,^[6]^ continuous reviews regarding CT are still required. The positive aspects of CT include increased patient satisfaction and diversity of treatment options.^[7–9]^ However, its limitations include a conflict between an MD and KMD due to lack of academic understanding, a concern about medical service overuse, and shortcomings of the medical fee system.^[10–13]^

The National Health Insurance System (NHIS) of Korea covers a prior medical fee only if a patient receives treatment from both an MD and a KMD for the same disease on the same day.^[14]^ For instance, if a patient is prescribed pain medication by an MD for LBP and then treated with acupuncture by a KMD for LBP on the same day, it is considered that the patient underwent duplicate treatments. Hence, the fee for the acupuncture treatment is not covered by the NHIS and can be an additional burden on the patient.

In addition, the consultant's fee, which is provided to medical institutions when CT is performed, is not reimbursed for outpatients but only counted for inpatients, 2 to 5 times per month.^[15]^ Therefore, the fee system for CT requires improvement for both patients and healthcare providers.^[16–18]^

Based on the above status, the Ministry of Health and Welfare had conducted a first-stage pilot project to investigate utilization rate and patient satisfaction with CT, applying NHIS cover for both WM and KM treatments for the same disease.^[19]^ It revealed high patient satisfaction and frequent ailments of CT.^[7]^

Adding the recognition of consultant fee, the second-stage pilot project is designed to evaluate the clinical and cost-effectiveness of CT.^[20]^ This pilot study is part of the Registry for Korean Medicine and Western Medicine Collaborative Treatment and evaluates the clinical and cost-effectiveness of CT for LBP, which is one of the frequent ailments treated by CT.

## Methods

2

### Study design and setting

2.1

Based on the International Society for Pharmacoeconomics and Outcomes Research's Good Research Practices dictates,^[21]^ the study is a multicenter and prospective observational comparative effectiveness research for the effectiveness of CT in patients with LBP. The patients with LBP are being recruited from 4 university-affiliated hospitals and 3 KM hospitals. A patient receives treatment according to their treatment plan. During or after the treatment, an 8-week study is conducted and a researcher assesses change in the patient's condition and cost of therapy thrice. In the final analysis, the merged data from the participants’ questionnaire responses, hospital medical records, and administrative data and Health Insurance Review and Assessment Service (HIRA) data will be compared between the CT and sole treatment (ST) groups. Figure 1 depicts the study design in a flow chart.

**Figure 1 F1:**
[figure not shown]
Flow chart of the study. CT = collaborative treatment, HIRA = Health Insurance Review and Assessment, ST = sole treatment.

### Participants

2.2

(1)Inclusion criteria1.Age ≥19 years and undergoing treatment at one of the institutions included in the study2.First-time visitor to the institution for LBP3.Voluntary informed consent(2)Exclusion criteria1.Participation in another trial2.Difficulties or anticipated difficulties in complying with the study schedule3.Difficulties or anticipated difficulties in understanding and/or responding to study questionnaires4.Difficulties with study participation, as judged by the researchers

### Participant consent and registration

2.3

A Patient who wishes to participate receives information regarding the study. Researchers explain to the participants that there is no relation between their participation and any provision of care, no obligation to participate, and no disadvantage if they choose not to participate or withdraw during the study course. After written informed consent is obtained, an MD or a KMD will judge the participant's eligibility, and those who meet the criteria are registered as study participants and enrollment numbers are assigned to anonymize them.

### Source, measurement, and management

2.4

Data will be collected from the participants’ questionnaire responses, hospital medical records, and administrative data, and the HIRA data.

The participants’ questionnaire includes demographic information, medical history, clinical assessment, and cost information. Demographic information consists of birth date, sex, occupation, income, and any private medical insurance. Medical history consists of past treatment history for LBP, and other diseases or conditions apart from LBP. Clinical assessment consists of assessment indices for LBP. Cost information obtained from this questionnaire includes data that would not be obtainable from both hospital medical records and administrative data and HIRA data, such as medical expenses not covered by NHIS, supplementary foods, and auxiliary equipments for LBP.

Hospital medical records and administrative data include the number of visits, the number times the patient undergoes CT, the expenditure at the institution for LBP, the length of study participation, the department that requested CT, the department that accepted CT, and the date of initiation of CT.

The HIRA data are used for investigating the treatment modality (CT or ST) and the duration of LBP treatment. Moreover, medical expenses, such as the expenses covered by NHIS, can be obtained from the HIRA data.

All data will be entered and managed using iCReaT, which is an electronic-case report form designed by the Korea National Institute of Health. As executive agency of this study, the Monitoring Center for Korean Medicine and Western Medicine Collaboration is involved in data management by monitoring the study process. Table 1 shows the study data collection schedule.

**Table 1 T1:**
[figure not shown]
Data collection schedule.

### Outcome measurement

2.5

#### Primary outcome measurement

2.5.1

Primary outcome is the evaluation of clinical effectiveness assessed from the change in the numeric rating scale (NRS), Oswestry Disability Index (ODI), EuroQol-5 dimension-5 level (EQ-5D-5L), and EuroQol-visual analog scale (EQ-VAS) scores.

The NRS^[22]^ converts pain intensity to numerical values, using a horizontal line between 0 (no pain) and 10 (greatest pain severity). The ODI^[23,24]^ measures the degree of daily life disability caused by LBP. The EQ-5D-5L^[24,25]^ measures the quality of life using questions on mobility, self-care, activity, pain intensity, depression, and anxiety. The EQ-VAS^[25]^ scores quality of life using a horizontal line.

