### Sample size rationale

2.6

The sample size was calculated by using the means (group 1 = 1.4, group 2 = 2.2) and standard deviations (sd 1 = 2.57, sd 2 = 2.76) from a previous study by NRS^[29]^ in the estimation equation^[30]^ via G-power program analysis (a 2-tailed, α = 0.05, β = 0.2). The result was 352, and the target number of inclusion was set at 360.

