### Statistical analyses

2.7

Outcomes will be compared between the main groups (CT and ST), which are stratified into 2 subgroups (acute or chronic^[31]^ and outpatient or inpatient^[32]^). The CT group is defined as those who receive treatments from both an MD and a KMD. The ST group is defined as those who receive only one form of treatment from either an MD or a KMD.

For analyzing categorical data, Chi-square tests and Fisher exact tests will be used. For analyzing continuous data, Student *t*-tests, analyses of variance, and Wilcoxon signed-rank tests will be used after normal distribution has been confirmed. For analyzing missing data, the per-protocol (PP) and intention to treat (ITT) will be used. In cases of missing completely at random data and missing at random data, as defined by Rubin,^[33]^ the ITT will be used to analyze missing values using a multiple imputation^[34]^ of the PP.

For all statistical tests performed in this study, a significance level of .05 and a 2-tailed confidence interval of 95% are set up. The Stata MP version 14 (Stata Corp LLC, Texas) and SAS version 9.4 (SAS Institute Inc, Cary, North Carolina) will be used for all statistical analyses.

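### Four unranked primary measures are each tested at .05, but the sample size covers only one NRS comparison

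*Protocol article*

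**What the plan says.** Section 2.5.1 (Primary outcome measurement) gives one primary outcome, clinical effectiveness, described as "assessed from the change in the numeric rating scale (NRS), Oswestry Disability Index (ODI), EuroQol-5 dimension-5 level (EQ-5D-5L), and EuroQol-visual analog scale (EQ-VAS) scores". All four scales are listed side by side, with no ranking and no visit attached.

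Section 2.7 (Statistical analyses) sets the error level: "For all statistical tests performed in this study, a significance level of .05 and a 2-tailed confidence interval of 95% are set up". It also states: "Outcomes will be compared between the main groups (CT and ST), which are stratified into 2 subgroups". The subgroups are acute or chronic, and outpatient or inpatient.

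Section 2.6 (Sample size rationale) uses means and standard deviations for NRS only, with a two-tailed α of 0.05 and β of 0.2: "The result was 352, and the target number of inclusion was set at 360".

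The Abstract says that "a researcher conducts investigations thrice, every 4 weeks", within an 8-week study, and section 2.1 confirms three assessments.

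**The concern.** The outcome section treats four scales as equally primary, while the sample size section treats NRS as the only one. With a flat .05 for every test and no statement of whether one scale or all four must show a difference, a significant result on any scale could be reported as a positive primary result. The 5% error rate and 80% power then describe a different analysis from the one the outcome section sets out.

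The Discussion part of the Abstract presents the results as a possible milestone for policy on collaborative care. A headline scale that can be picked after the data are seen weakens that use. It is also an avoidable weakness, separate from the confounding that the article already acknowledges.

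**Working it through.** **Inputs.** From section 2.6: NRS means 1.4 and 2.2 (difference 0.8), standard deviations 2.57 and 2.76, two-sided α 0.05, power 0.80, stated result 352, target 360. From section 2.5.1: four measures. From section 2.7: .05 for each test. Assumptions that are not in the document: 1:1 group sizes, equal correlation r between the four test statistics, and success on any one measure.

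**Step 1: reproduce the sample size.** Variance = (2.57² + 2.76²)/2 = (6.6049 + 7.6176)/2 = 7.111, so SD = 2.667.
n per group = 2 × (1.960 + 0.842)² × 7.111 / 0.8² ≈ 174.4, rounded up to 175, or 350 in total by the normal approximation.
With the noncentral t distribution, 175 per group gives power 0.799 and 176 per group gives 0.801, so 352 in total. The stated figure reproduces exactly. It is the size for one NRS test at the full 0.05.

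**Step 2: false positives over four measures, one visit, no true difference.** Under independence, either direction: 1 − 0.95⁴ = 0.185. In CT's favour only: 1 − 0.975⁴ = 0.096. With correlation, by multivariate normal simulation (400,000 draws):

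| Assumed r | Either direction | In CT's favour |
|---|---|---|
| 0 | 18.5% | 9.6% |
| 0.3 | 17.4% | 8.8% |
| 0.5 | 15.6% | 7.8% |
| 0.7 | 13.1% | 6.6% |
| 0.9 | 9.4% | 4.7% |
| single test | 5% | 2.5% |

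**Step 3: both follow-up visits open.** Three assessments every 4 weeks over 8 weeks suggest baseline, week 4 and week 8, hence two changes per scale and eight tests. This is an inference; the data collection table is not visible.
- All eight independent: 1 − 0.95⁸ = 0.337. Independence is implausible for the same scale in the same patients.
- One common correlation of 0.3, 0.5 or 0.7 among all eight: 30.1%, 25.0% or 19.1%.
- Between-measure r of 0.3 to 0.7 with a between-visit correlation of 0.5 or 0.7: about 21-30% in either direction, and about 10-15% in CT's favour.

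**Step 4: cost of protecting four tests with the planned patients.** Bonferroni level: 0.05/4 = 0.0125, two-sided critical value 2.498.
At 180 per group the standard error is 2.667 × √(2/180) = 0.281, and 0.8/0.281 = 2.85. Power ≈ Φ(2.85 − 2.50) ≈ 0.64 by the normal approximation and 0.63 by noncentral t. At the full 0.05 it is 0.81.
For 80% power at 0.0125: 2 × (2.498 + 0.842)² × 7.111/0.64 ≈ 248 per group, 496 in total.

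**The case against.** The strongest reply is that this is a condensed article. Success rules, the primary visit and multiplicity methods are often left to a statistical analysis plan, and a general .05 sentence may state only a nominal level. That stands for the missing visit and the missing rule taken alone. It does not answer the core point: the article itself fixes four unranked primaries, a .05 level for all tests and a sample size for NRS alone, and those statements do not fit together.

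Other objections stand and limit the claim:

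- **Direction.** A reader might infer that the chance of falsely declaring CT effective is well above 5%. At one visit the figures do not support that: about half of the two-sided errors favour sole treatment, and errors in CT's favour run from 4.7% to 9.6%. That is still about two to four times the nominal 2.5%.
- **Eight primary tests.** A reader might count eight tests as fixed by the plan. The article states three assessments and does not say that both follow-up changes are tested as primary.
- **Correlation.** 18.5% is the independence figure. The EQ-5D-5L includes a pain item and two of the scales measure quality of life, so positive correlation is likely and the lower rows are more realistic.
- **Success rule.** If all four scales had to be significant, the false-positive rate would not exceed 5%. The article does not say this and gives no power for it.
- **Subgroups.** A reader might put subgroup power at 52%. That assumes 90 against 90, an even split that the document does not give. Section 2.7 does not call the subgroup results primary either.

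The study is observational and part of a pilot project, and confounding is conceded as a limitation. That lowers the weight of any single p-value, but it is no reason to leave the primary outcome open.

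**Conclusion.** The point holds in limited form: the primary outcome, the test level and the sample size are mutually inconsistent as written. If any one of four measures may count as success, the two-sided familywise error at one visit is 18.5% under independence and about 17% down to 9% for r = 0.3 to 0.9. In CT's favour it is about 5-10% against 2.5%. If both follow-up visits are open, the two-sided figure is about 19-30% for r = 0.3 to 0.7.

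The stated power covers one NRS test at 0.05; under Bonferroni over four measures it is about 63% with 360 patients. The error figures rest on the any-one rule and on assumed correlations, the two-visit figures also on the inferred visit schedule, and the power figures on equal groups.

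**What to change.** Name change in NRS at one stated visit, for example the final week 8 visit, as the single primary outcome. This agrees with the sample size calculation and leaves 352 and 360 unchanged. Section 2.6 does not say at which visit the NRS means apply or whether they are change scores, so state that the inputs suit the visit chosen.

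Make ODI, EQ-5D-5L and EQ-VAS secondary, tested in a prespecified fixed order or with Holm, and treat the other follow-up visit as supportive. Label the acute/chronic and inpatient/outpatient comparisons exploratory.

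If all four measures are to stay primary, state whether one or all must succeed and redo the sample size. With Bonferroni and the NRS inputs this means 496 patients.

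The preferred change needs no extra patients or data: protocol and analysis wording plus a registry update, made before outcomes are compared. The downside is that fewer results can be called primary.

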#### Secondary outcome measurement

2.5.2

Secondary outcome is the evaluation of cost-effectiveness assessed from the cost per quality-adjusted life-years (QALYs), the incremental cost-effectiveness ratio (ICER), and the cost-effectiveness acceptability curve (CEAC).

The cost per QALYs is estimated based on the area under the curve method^[26]^ for each participant's quality of life data (e.g., the EQ-5D-5L and the EQ-VAS). The ICER represents the economic value of an intervention compared with an alternative. This is calculated by dividing the difference in total incremental cost by the difference in the chosen measure of health outcome or incremental effect.^[27]^ In CEAC, the horizontal axis represents the cost-effectiveness per ICER, and the vertical axis represents the probability of meeting that cost-effectiveness.^[28]^

### Sample size rationale

2.6

The sample size was calculated by using the means (group 1 = 1.4, group 2 = 2.2) and standard deviations (sd 1 = 2.57, sd 2 = 2.76) from a previous study by NRS^[29]^ in the estimation equation^[30]^ via G-power program analysis (a 2-tailed, α = 0.05, β = 0.2). The result was 352, and the target number of inclusion was set at 360.

### Statistical analyses

2.7

Outcomes will be compared between the main groups (CT and ST), which are stratified into 2 subgroups (acute or chronic^[31]^ and outpatient or inpatient^[32]^). The CT group is defined as those who receive treatments from both an MD and a KMD. The ST group is defined as those who receive only one form of treatment from either an MD or a KMD.

For analyzing categorical data, Chi-square tests and Fisher exact tests will be used. For analyzing continuous data, Student *t*-tests, analyses of variance, and Wilcoxon signed-rank tests will be used after normal distribution has been confirmed. For analyzing missing data, the per-protocol (PP) and intention to treat (ITT) will be used. In cases of missing completely at random data and missing at random data, as defined by Rubin,^[33]^ the ITT will be used to analyze missing values using a multiple imputation^[34]^ of the PP.

For all statistical tests performed in this study, a significance level of .05 and a 2-tailed confidence interval of 95% are set up. The Stata MP version 14 (Stata Corp LLC, Texas) and SAS version 9.4 (SAS Institute Inc, Cary, North Carolina) will be used for all statistical analyses.

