## Discussion

3

In several earlier studies regarding CT, we found that the sample sizes were small and the type of KM used in CT was designated. In addition, the assessment of the effectiveness of CT mostly focused on “cooperation in the treatment”; there are few reports on the “cooperation in the diagnosis and examination.”^[17,35]^ Our study design overcomes these limitations with a relatively large sample size, no restriction on the type of KM, and by including cooperation at all clinical steps, such as examination, diagnosis, and treatment to reflect a real-world scenario.

There are a few limitations to this study protocol. First, in an observational study, researchers do not intervene in the allocation process for randomization, and there may be confounding factors. Thus, this would be a limitation to confirming a cause and effect relationship. Second, as the institutions that actively implement CT will be participating in this study, they will not be representative of the general status of CT in Korea.

Nevertheless, the clinical implications of this study are significant. By ensuring that the KM treatments are carried out without the intervention of the researchers, we can reflect a real-world clinical situation in which all forms of KM treatments, such as acupuncture, moxibustion, herbal medicine, and chuna, may be used. In addition, this study can provide basic information on complementary medicine for population health and healthcare economics.

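### For a non-randomised CT versus ST comparison, the plan names no adjustment for confounders or institution beyond two subgroup strata and change scores

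*Protocol article*

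**What the plan says.** The Study design and setting section states that "the study is a multicenter and prospective observational comparative effectiveness research for the effectiveness of CT in patients with LBP". Treatment is not allocated by the study: "A patient receives treatment according to their treatment plan". On sites: "The patients with LBP are being recruited from 4 university-affiliated hospitals and 3 KM hospitals", which makes seven institutions.

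The Statistical analyses section sets out the comparison: "Outcomes will be compared between the main groups (CT and ST), which are stratified into 2 subgroups". The two stratifying factors are acute or chronic, and outpatient or inpatient. For methods: "For analyzing categorical data, Chi-square tests and Fisher exact tests will be used". For continuous data it lists Student t-tests together with "analyses of variance, and Wilcoxon signed-rank tests will be used after normal distribution has been confirmed". It names no covariate model, propensity score, matching, weighting or institution term.

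The primary outcomes are changes in NRS, ODI, EQ-5D-5L and EQ-VAS. The data section lists likely confounders: "Demographic information consists of birth date, sex, occupation, income, and any private medical insurance". It also lists past treatment for low back pain and other conditions. None of these is given a role in the analysis. The Discussion concedes that "researchers do not intervene in the allocation process for randomization, and there may be confounding factors", and treats this as a limit on causal conclusions.

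**The concern.** The study exists to judge the comparative clinical and cost-effectiveness of CT. Patients who receive CT do so under their own treatment plan, so they may differ from ST patients in severity, history, means, insurance cover and hospital. A t-test on the two groups asks whether CT users changed differently from ST users. That answers the effectiveness question only if the groups are alike on what drives outcome. If they are not, the difference is biased, the nominal 5% error rate does not apply to the effectiveness hypothesis, and a larger sample does not help because the bias does not shrink with n. The same bias would pass into costs, QALYs and the ICER.

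Institution is a further route. If the share of CT differs among the seven sites, site differences in outcome or cost enter the CT–ST contrast. The document gives no CT share by site, so this part cannot be sized.

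**Working it through.** **Inputs from the Sample size rationale:** means 1.4 and 2.2 (difference 0.8 NRS points), SDs 2.57 and 2.76, two-sided α = 0.05, power 80%, result 352, target 360.

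**Step 1: reproduce the plan's figure.**
- Pooled SD = √[(2.57² + 2.76²)/2] = 2.667, so d = 0.8/2.667 = 0.300.
- The normal approximation gives 175 per group, 350 in total.
- The exact noncentral-t calculation gives 176 per group, 352 in total, with power 80.1%. At 180 per group power is 81.0%.

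The stated 352 is therefore reproduced exactly as a plain two-sample t-test with equal groups. Equal allocation is not stated, but the match implies it. The sample size thus rests on the same kind of unadjusted comparison that the analysis section lists.

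**Step 2: effect of confounding on that test.** Assumptions not in the document: no true CT effect, 180 per group, and a single prognostic factor that differs between groups by a given number of SDs and correlates with NRS change as shown. The SD of 2.667 is taken to apply to change scores.

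- Bias = imbalance (in SD) × correlation × 2.667.
- Noncentrality = (bias/2.667) × √(180 × 180/360) = (bias/2.667) × √90, where √90 = 9.487.
- Low case: 0.2 × 0.3 × 2.667 = 0.16.
- High case: 0.4 × 0.5 × 2.667 = 0.53.

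| Bias (NRS points) | Share of planned 0.8 | Noncentrality | False-positive rate |
|---|---|---|---|
| 0.16 | 20% | 0.57 | 8.8% |
| 0.30 | 37.5% | 1.07 | 18.6% |
| 0.40 | 50% | 1.42 | 29.5% |
| 0.53 | 67% | 1.90 | about 47% |

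**Step 3: a cross-check with a binary factor (also assumed).** A factor worth 1 to 2 NRS points and 20 percentage points more common in one group gives a bias of 1 × 0.2 = 0.2 to 2 × 0.2 = 0.4 points. The false-positive rate is then 10.9% to 29.5%, inside the range above.

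**Step 4: what adjustment does to precision.** If covariates explain a share Rt² of treatment choice and Ry² of outcome variance, the required total is about 350 × (1 − Ry²)/(1 − Rt²). Over assumed ranges of Rt² from 0.1 to 0.3 and Ry² from 0 to 0.3:
- Best case: 350 × 0.7/0.9 ≈ 273, with power of about 90% at 360.
- Worst case: 350 × 1/0.7 = 500, with power of about 66% at 360.

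**The case against.** The strongest reply is that a condensed article commonly leaves covariate lists and propensity models to a full protocol or analysis plan, and neither is shown. Collecting income, insurance and history is compatible with planned adjustment, and a t-test sample size does not bind the analysis model. An unseen plan may indeed add adjustment. But this article does not leave the analysis open. It lists its tests, software, significance level and missing-data approach, and it raises confounding without naming any analytic remedy. In an observational effectiveness study, control of confounding is the central analytic choice, so what is stated can fairly be questioned.

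A reader might go further and infer that the comparison is wholly unadjusted and that any difference in case mix will be presented as a CT effect. The document does not support that:
- Comparisons within the acute/chronic and outpatient/inpatient strata control those two factors.
- Analysis of variance is not restricted to one-way models and could include the strata.
- Change scores partly account for baseline level, although regression to the mean can leave bias when baselines differ.
- The Discussion itself limits the causal reading.

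The objection to the numbers also stands in part. The imbalances, correlations and equal split are assumed, and the upper case needs a large imbalance and a strong correlation together, left untouched by the strata. The sample size section does not say whether its SDs are for change scores or for levels.

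**Conclusion.** The point holds in limited form. The study is not randomised, and beyond two subgroup strata and change scores the stated analysis specifies no adjustment for confounders or institution. No estimate pooled over the strata is described, so the overall CT–ST difference remains open to confounding. Acknowledging this in the Discussion does not correct it.

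A bias of 0.16 to 0.53 NRS points, 20% to 67% of the planned difference, would raise the false-positive rate from 5% to about 9% to 47%. This is an illustration that rests on the assumptions listed in the working. A reader might take 47% as the expected error rate, but nothing in the document establishes how large the imbalances will be.

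**What to change.** Name one adjusted analysis in advance as the primary comparison. One suitable form is a linear or repeated-measures model of NRS at weeks 4 and 8 with:
- group, visit and group-by-visit;
- first-assessment score, acute/chronic and inpatient/outpatient;
- age, sex, income, private insurance, past treatment for low back pain and comorbidity;
- institution.

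Propensity-score overlap weighting is an alternative, but it targets a different population when effects vary. Choose one method as primary and keep the other as a sensitivity analysis.

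The Study design section allows the eight-week period to run while treatment is under way or after it has ended. First-assessment scores should therefore be adjusted for as baseline only where they precede treatment, and the plan should say how this is determined.

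Report covariate balance between CT and ST, keep the unadjusted tests as descriptive, and apply the same adjustment to ODI, EQ-5D-5L, EQ-VAS, costs and QALYs.

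**Cost:** analysis-plan wording and a little more programming, with no new data. Precision falls if treatment group aligns strongly with site or covariates. Over the assumed ranges in the working, power at 360 would be about 66% to 90%, so the sample size statement should be revisited alongside the model.
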